#### Interim analyses {21b}

There are no planned interim analyses.

#### Methods for additional analyses (e.g. subgroup analyses) {20b}

We will explore whether outcomes are different between groups for minimisation variables (age, gender, site) and for type of surgery (right v left side colectomy) and by enhanced recovery compliance indicators. Additional planned sub-group analysis will be documented in the statistical analysis plan (SAP) or defined as post hoc analyses.

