**Methods:**

United Kingdom (UK) multi-centre double blind placebo-controlled randomised controlled trial in 562 patients undergoing elective minimally invasive colorectal resection. IV lidocaine or placebo will be infused for 6–12 h commencing at the start of surgery as an adjunct to usual analgesic/anaesthetic technique. The primary outcome will be return of GI function.

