
There is no specific therapy for postoperative ileus; treatment is supportive until GI function returns spontaneously. Alvimopan (Entereg®) is a selective μ-opioid receptor antagonist evaluated in a number of North American randomised controlled trials (RCTs) where it has been shown to be of benefit in reducing incidence of postoperative ileus [5]. However, it has not gained widespread use due to cost and concerns regarding its cardiac side-effect profile and is not licensed for use in the UK.

Lidocaine, familiar as a local anaesthetic, has analgesic and anti-inflammatory effects when administered systemically by intravenous (IV) infusion and hence has been repurposed as an anaesthetic adjunct in abdominal surgery. Studies in various surgical procedures have shown reduced early postoperative pain scores and reduced opioid analgesia requirements. There also seems to be a consistent benefit on measures of GI function recovery, including time to first flatus, time to first bowel movement, postoperative nausea and risk of postoperative ileus. However, the limitation of meta-analysis in this area is the considerable heterogeneity of studies included: a variety of surgical procedures, a mix of open and laparoscopic techniques, inconsistent lidocaine dose/treatment duration, inconsistent perioperative management protocols and study endpoints [6–8]. There are only three published RCTs of intravenous lidocaine in laparoscopic colectomy, comprising a total of 181 patients. Two were conducted in Europe and reported length of stay consistent with modern NHS practice (3 to 5 days) [9, 10]. Both studies reported reduced analgesic requirements, faster return of gut function and a 1-day reduction in median length of stay. The third study was conducted in South Korea and found a trend towards faster GI recovery but no statistically significant benefit. However, perioperative management practices were not consistent with NHS norms and the excessive median length of stay of 9 days makes this study difficult to interpret [11].

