#### Secondary objectives

The secondary objectives are to compare the proportion of participants randomised to IV lidocaine or placebo in respect of:
GI-2 recovery endpointThe rate of prolonged postoperative ileusPostoperative nausea and vomitingAnalgesia requirementsQuality of postoperative recovery using multi-dimensional patient-reported outcome tools and quality of life tools.

Additional secondary objectives include assessing whether perioperative intravenous lidocaine during colorectal surgery is cost-effective relative to current standard of care (colorectal surgery without intravenous lidocaine) and measuring the impact of variation in peri-operative care from Enhanced Recovery After Surgery guidelines.

The tertiary objectives are to compare the proportion of participants randomised to IV lidocaine or placebo in respect of:
Total length of stay30- and 90-day mortalityUnplanned re-admissions within 30 days of hospital dischargeReoperation/major complications (Clavien-Dindo classification grade 3 and above) [15]Qualitative analysis of recovery beyond hospital (General Practitioner (GP) visits, district nurse visits).

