#### Primary outcome

The primary outcome is achievement (yes/no) of GI-3 recovery (a composite endpoint defined as the achievement of both of the following two events: tolerating diet without significant nausea or vomiting for three consecutive meals; AND passage of flatus OR stool) at 72 h after the start of operation.

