### Recruitment {15}

Eligible individuals are identified by their usual clinical team from planned elective operating lists and given a patient information sheet. Eligibility is confirmed, consent received, baseline details collected, and randomisation performed pre-operatively, where possible, at routine hospital visits.

As noted above (in the “Who will take informed consent? {26a}” section) where a face-to-face visit is not possible to carry out the recruitment procedures, participants can complete the consent form at home and either post it back to the research team or bring it into hospital with them when they are admitted for surgery. In such cases, eligibility is confirmed, baseline details collected, and randomisation performed pre-operatively.

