### Data collection and management

#### Plans for assessment and collection of outcomes {18a}

Data are collected at baseline and at 1, 2, 3, 4, 5, 6 and 7 days after surgery, at discharge from hospital and at 30 and 90 days after surgery. The schedule for data collection is summarised in Table 1.

**Table 1 Tab1:** Schedule for data collection

Assessment	Recruitment/baseline	POD 1	POD 2	POD 3	Daily from POD 4 until discharge	POD 7	Discharge	30 days	90 days
Assessment of eligibility criteria	✓								
Written informed consent	✓								
Pregnancy test (where applicable)									
Demographic data, contact details	✓								
Clinical history/past medical history	✓								
Drug history esp. laxatives	✓								
Height	✓								
Weight	✓	✓							
p-POSSUM	✓	✓ (part)						✓ (part)	
Operation type		✓							
Duration of operation		✓							
Blood loss (ml)^a^		✓							
OBAS score	✓	✓	✓	✓	✓	✓			
QoR score	✓	✓	✓	✓	✓	✓		✓	
PONV score		✓	✓	✓	✓				
EQ-5D-5L	✓	✓	✓	✓	✓	✓		✓	✓
CRP^b^	✓		✓	✓					
Time to first flatus			✓	✓	✓				
Time to first bowel movement			✓	✓	✓				
Time to tolerating solid food			✓	✓	✓				
antiemetic dose total up to 72 h							✓		
Total number of episodes vomiting		✓	✓	✓					
Total opioid consumption in-hospital up to 72 h							✓		
ERAS protocol compliance		✓	✓	✓					
Achievement of medical criteria for discharge Y/N				✓	✓				
Patient-reported readiness for discharge				✓	✓				
Length of stay (days)							✓		
Complications							✓	✓	
Unplanned readmissions								✓	
Mortality							✓	✓	✓
Adverse events		✓	✓	✓	✓	✓		✓	
Concomitant medications	✓	✓	✓	✓	✓	✓		✓	

^a^Millilitres

^b^C-reactive protein

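### The planned subgroup analysis by enhanced recovery compliance uses a factor recorded only on POD 1–3, after treatment, so its within-level comparisons are open to bias

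*Protocol article*

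**What the plan says.** The protocol article's section {20b} names its exploratory subgroup factors: the three minimisation variables (age, gender, site), right versus left colectomy, and "by enhanced recovery compliance indicators". It then adds: "Additional planned sub-group analysis will be documented in the statistical analysis plan (SAP) or defined as post hoc analyses". Only further subgroups are left to the SAP; the compliance subgroup is already chosen here.

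Four other places bear on it:

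- **When compliance is recorded.** In Table 1 (section {18a}) the row "ERAS protocol compliance" is ticked on POD 1, POD 2 and POD 3, with no tick at baseline.
- **Its other role.** The list of secondary outcomes includes compliance with the enhanced recovery (ERAS) protocol.
- **Why it is of interest.** A secondary objective is "measuring the impact of variation in peri-operative care from Enhanced Recovery After Surgery guidelines".
- **Order of events.** Section {15} has "randomisation performed pre-operatively". The abstract says "IV lidocaine or placebo will be infused for 6–12 h commencing at the start of surgery". The primary outcome, GI-3 recovery, is assessed "at 72 h after the start of operation".

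**The concern.** A subgroup comparison of randomised arms is fair when the factor could not have been altered by the allocation. Age, gender and site meet that condition, and side of colectomy follows the planned operation. Compliance as scheduled does not clearly meet it: it is recorded after the drug has been given, over the same three days in which GI-3 is decided, and the article itself treats it as something to compare between arms.

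The article also supplies a route by which lidocaine could move it. In the background section: "Studies in various surgical procedures have shown reduced early postoperative pain scores and reduced opioid analgesia requirements". A patient with less pain and less opioid may follow a recovery pathway more easily. If so, compliers on lidocaine include some patients who would not have complied on placebo, and the two groups of compliers are no longer alike in prognosis. The same holds for non-compliers.

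At stake is how one exploratory result is read. Because compliance stands in the same list as baseline factors, a reader would give its within-level effects the same trust. Since variation in ERAS care is a stated objective, the result is likely to be reported.

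**Working it through.** **1. The plan's own figures.** The article gives no figure for this subgroup, so there is none to reproduce. The sample-size section supplies the anchor: non-return of gut function 40% versus 26.8%, that is GI-3 achieved in 60% versus 73.2%, a difference of 13.2 points. Those inputs reproduce the stated total with a continuity correction: 564 for 40% v 26.8% and 562 for 30% v 18%, against 562 stated. Nothing there is disputed.

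**2. Timing.** Randomisation is before surgery; the infusion starts with surgery and lasts at most 12 h; compliance is recorded on POD 1–3; GI-3 is judged at 72 h. The factor therefore follows the treatment and overlaps the outcome window.

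**3. Illustrative model A (all assumptions mine).**

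- Latent recovery L is standard normal on placebo. GI-3 is achieved when L > −t, with t = Φ⁻¹(0.60) = 0.253.
- Lidocaine shifts L by the same amount in everyone: d = Φ⁻¹(0.732) − Φ⁻¹(0.60) = 0.619 − 0.253 = 0.366.
- A patient complies when ρL + √(1 − ρ²)·e > 0, with e independent standard normal and ρ = 0.5 or 0.7. Compliance on placebo is 50%.
- *Measured after treatment:* the shifted L enters the compliance rule, so compliance on lidocaine is Φ(ρd) = Φ(0.183) = 57% or Φ(0.256) = 60%.
- *Fixed before treatment:* the unshifted L enters the rule, so compliance is 50% in both arms. This is the proper comparator.

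Percentage achieving GI-3, from the bivariate normal distribution:

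| ρ | Stratum | Placebo | Lidocaine, stratifier after treatment | Lidocaine, stratifier before treatment | Effect after | Effect before | Shrinkage |
|---|---|---|---|---|---|---|---|
| 0.5 | compliers | 76.1 | 85.2 | 86.7 | 9.1 | 10.6 | 1.5 |
| 0.5 | non-compliers | 43.9 | 57.2 | 59.7 | 13.3 | 15.8 | 2.5 |
| 0.7 | compliers | 83.7 | 90.0 | 92.6 | 6.3 | 8.9 | 2.6 |
| 0.7 | non-compliers | 36.3 | 47.9 | 53.8 | 11.6 | 17.5 | 5.9 |

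On the log-odds scale of the planned logit model, compliers and non-compliers fall from 0.72 and 0.64 to 0.59 and 0.53 (ρ = 0.5), and from 0.89 and 0.71 to 0.56 and 0.48 (ρ = 0.7).

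**4. Illustrative model B (simulation, 4 million patients per scenario).** A standard normal factor U acts on both variables: logit P(non-return) = −0.48 − U + δ·T and logit P(comply) = U + γ·T, where T = 1 for lidocaine. Control non-return is 40%. Effects below are differences in non-return, in points, so a positive value makes lidocaine look worse.

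| Drug effect | Compliance, placebo v lidocaine | Compliers | Non-compliers |
|---|---|---|---|
| none (δ = 0) | 50% v 50% | −0.1 | −0.1 |
| none | 50% v 58% | +1.4 | +1.5 |
| none | 50% v 66% | +2.6 | +3.1 |
| δ = −0.72 (overall about −13.3) | 50% v 50% | −11.9 | −14.6 |
| δ = −0.72 | 50% v 58% | −10.8 | −13.3 |
| δ = −0.72 | 50% v 66% | −9.8 | −12.0 |

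Against the row where lidocaine leaves compliance alone, the shrinkage is 1.0 and 1.3 points at 58%, and 2.0 and 2.6 points at 66%. When U is removed from the compliance equation, the strata give about 0 with no drug effect and about −13.4 each with one, whatever γ is.

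Both models say the same: the effect is attenuated in both strata, and only when both links are present.

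**The case against.** **The indicators are not listed.** The article names no ERAS item. A POD 1 form can carry earlier information: Table 1 also ticks operation type, duration and blood loss at POD 1. Some compliance items may therefore have been fixed before the infusion, and the full protocol or SAP may define them. This stands, and it limits the point to indicators that treatment can change. It does not remove the point, because section {20b} chooses the factor without any such restriction.

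**Neither link is quantified.** Bias needs lidocaine to change compliance, and compliance to share causes with GI-3. Both are plausible from the article's background, but it gives no figure for either. Model A in particular passes the whole drug effect into compliance. So the subgroup effects are open to bias, not shown to be biased.

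**The analysis is exploratory.** This also stands, and it limits the importance of the point.

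**A stronger reading fails.** A reader might see the unequal effects in model A (9.1 v 13.3, or 6.3 v 11.6 points), call the gap of 4–5 points spurious, and conclude that the analysis would manufacture an interaction, such as lidocaine appearing to work only with or only without good enhanced recovery care. The check does not support that. A stratifier fixed before treatment gives a larger gap: 15.8 − 10.6 = 5.2 and 17.5 − 8.9 = 8.6 points. The gap arises because a uniform latent shift gives a smaller risk difference where recovery on placebo is already high. On the planned logit scale the odds ratios are close (1.80 v 1.71, and 1.75 v 1.61), and no stratum loses its effect. With no drug effect, model B moves both strata almost equally.

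**Conclusion.** The point holds in limited form. Section {20b} sets a factor recorded only on POD 1–3, and listed as an outcome, beside factors the allocation cannot alter. Arm comparisons within levels of any indicator that lidocaine can change are not protected by randomisation.

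The size is illustrative only. With a latent correlation of 0.5 and the drug effect passing into compliance, both strata understate the effect by about 1.5–2.5 points; with 0.7, by about 2.6–6 points. If lidocaine leaves compliance unchanged, or compliance is unrelated to recovery, the bias is about zero. A false interaction is not shown. The primary intention-to-treat analysis is unaffected, so this is an advisable correction to an exploratory analysis and no threat to the main result.

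**What to change.** Amend section {20b}, and carry the same wording into the SAP:

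- Restrict the enhanced recovery subgroup to ERAS items fixed before the infusion starts, or to each centre's compliance computed from pre-trial data. Because the trial is double blind, items completed between randomisation and the infusion are also safe.
- Report POD 1–3 compliance by arm, as the secondary outcome it already is.
- If arms are still compared within levels of postoperative indicators, to serve the objective on variation in care, label that analysis as non-randomised and descriptive.

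The cost is analysis wording only; no data collection or sample size changes. The downside is that fewer compliance items can enter the subgroup. The centre-level option would need pre-trial data that the article does not mention, and would overlap with the existing subgroup by site.

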#### Methods in analysis to handle protocol non-adherence and any statistical methods to handle missing data {20c}

We do not anticipate any missing data due to the short timeframe of the primary outcome. However, should we observe substantial missing data, we will use multiple imputation and pattern mixture methods to explore the robustness of treatment effect estimates.

#### Plans to give access to the full protocol, participant level-data and statistical code {31c}

The full protocol is available as a supplement. Non-identifiable participant-level data may be available on request to the chief investigator (CI), [name] ([contact]).

### Oversight and monitoring

#### Composition of the coordinating centre and trial steering committee {5d}

The immediate trial team (CI, trial manager, data coordinator) meets every fortnight. On a monthly basis, the immediate team is joined by the wider trial team (statistician, health economist). A project management group (PMG) and trial steering committee (TSC) oversee the project. The PMG meets every 3 months and comprises the CI, grant holders and the trial office staff.

The TSC meets approximately every 6 months and includes an independent chair, clinical and methodological expertise and lay representative. Members of the PMG also attend the meetings of the TSC. Roles of the TSC are documented in the TSC charter, which all independent members have signed up to.

#### Composition of the data monitoring committee, its role and reporting structure {21a}

The data monitoring committee (DMC) meets approximately every 6 months to oversee the safety of participants in the trial. It includes an independent chair and independent members with clinical and methodological expertise. The CI, trial manager and other members of the PMG may attend the open session of the DMC. The DMC reports to the chair of the TSC. Roles are documented in the DMC charter, which all independent members have signed up to.

#### Adverse event reporting and harms {22}

Adverse events (AEs) will be identified and recorded from the time a participant signs the consent form to take part in the study until the 30th post-operative day. They will be asked about AEs daily during their admission, and during the 7- and 30-day telephone calls. When an AE occurs, it is the responsibility of the investigator, or another suitably qualified physician in the research team to review documentation related to the event. Relevant information will be recorded on the AE log and a serious adverse event (SAE) form if required—the specific requirements for recording events in ALLEGRO are described in Table 2 below.

**Table 2 Tab2:** Event recording

Event	If the event is thought to be an adverse reaction	If the event is not thought to be an adverse reaction
Lidocaine toxicity within 2 h of infusion	Record on adverse event log (SAR^a^ if meets criteria for serious)	n/a
Transient events common after surgery (listed in the protocol as: pyrexia; anorexia, nausea, vomiting, constipation, pain; raised inflammatory markers; minor wound infections; dizziness; transient biochemical derangement e.g. hypokalaemia, hyponatraemia, hypomagnesaemia, hypophosphataemia, hypocalcaemia; transient self-limiting confusional state)	Record on adverse event log	Recorded on adverse event log
Complications of surgery Clavien-Dindo grade 1/2	Record on adverse event log	Recorded on adverse event log
Complications of surgery Clavien-Dindo grade 3+	Record as SAR/SUSAR; report to sponsor within 24 h of becoming aware	Record as outcome data on CRF^b^
Prolongation of admission for social reasons	n/a	Record as outcome data on CRF
Death	Record as SAR/SUSAR; report to sponsor within 24 h of becoming aware	Record as SAE; report to sponsor within 24 h of becoming aware

^a^Serious adverse reaction

^b^Case report form

The investigator (or delegate) is responsible for assessing each AE using standard definitions for severity, seriousness, causality (relatedness to the IMP) and (if the event is assessed as related to the IMP) whether it is expected or unexpected based on information contained within the Summary of Product Characteristics for lidocaine. The sponsor is responsible for notifying the regulatory authority and ethics committee of suspected unexpected serious adverse reactions SUSARs within defined timelines.

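### Table 2 gives suspected reactions among transient events and Clavien-Dindo grade 1/2 complications a log-only route, at odds with the per-event seriousness assessment below it

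*Protocol article*

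**What the plan says.** All the relevant text is in the Protocol article, Adverse event reporting and harms {22}.

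- **Above the table.** One sentence covers both documents that a site may complete: "Relevant information will be recorded on the AE log and a serious adverse event (SAE) form if required". It then continues: "the specific requirements for recording events in ALLEGRO are described in Table 2 below".
- **Table 2, column for events thought to be an adverse reaction.** The lidocaine-toxicity row reads "Record on adverse event log (SAR^a^ if meets criteria for serious". The rows for Clavien-Dindo grade 3+ and for death read "Record as SAR/SUSAR; report to sponsor within 24 h of becoming aware". The row that begins "Transient events common after surgery (listed in the protocol as: pyrexia; anorexia, nausea, vomiting, constipation, pain; raised inflammatory markers; minor wound infections; dizziness" and the row "Complications of surgery Clavien-Dindo grade 1/2" each call for an entry on the adverse event log and carry no condition.
- **Below the table.** The investigator assesses each adverse event for severity, seriousness and causality and, where it is related to the study drug, expectedness against the product information. Then: "The sponsor is responsible for notifying the regulatory authority and ethics committee of suspected unexpected serious adverse reactions SUSARs within defined timelines".

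**The concern.** The table treats suspected reactions in neighbouring rows differently. One log row has the qualifier "if meets criteria for serious"; the other two do not. In those two rows the action is the same whether or not the event is thought to be a reaction, so the causality judgement has no effect on how the event is recorded. The paragraph below asks for exactly the judgements that identify a SAR or SUSAR, but says nothing about where the site records the result or how soon it tells the sponsor. Only the table does that.

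The stake is safety reporting. The sponsor can notify only what it has been told about. If a site takes the table as complete, a serious suspected reaction in either row could reach the sponsor late, or not as a SAR at all, and the trial's count of serious reactions would be too low. The primary and secondary outcome analyses are not affected.

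**Working it through.** No arithmetic bears on this beyond counting rows. The check sets the rows and the surrounding text side by side.

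**Step 1. Classify the six rows by their action for a suspected reaction.**

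| Row | Action for a suspected reaction | Seriousness condition | 24 h report to sponsor stated |
|---|---|---|---|
| Lidocaine toxicity within 2 h | Log; SAR if serious | Yes | No |
| Transient post-surgical events | Log | No | No |
| Clavien-Dindo grade 1/2 | Log | No | No |
| Clavien-Dindo grade 3+ | SAR/SUSAR | Not needed, goes direct | Yes |
| Prolonged admission, social reasons | Not applicable | – | – |
| Death | SAR/SUSAR | Not needed, goes direct | Yes |

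Count: 1 conditional + 2 log-only + 2 direct + 1 not applicable = 6. The gap is in two rows. The 24 h clause is also missing from the toxicity row.

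**Step 2. Does the text above the table supply the route?** It mentions an SAE form where one is required, with no event type excluded. The same sentence then names Table 2 as the specific requirements. The natural reading is that Table 2 says when the form is required, and in these two rows it does not ask for one. A looser reading, in which the form is a separate general duty, is possible. The wording does not settle it.

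**Step 3. Does the text below the table supply it?** It supplies the assessment, since each adverse event is judged for seriousness with no row exempt. It does not supply the site's action once an event is judged serious and related. The sponsor's duty to notify comes after that action.

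**Step 4. Can a serious suspected reaction fall in these rows?** The article does not list its criteria for serious, so this step rests on an assumption: that prolonged admission counts. The table has a separate row for prolongation on social grounds, which makes most sense if other prolongation can count. The Abstract links delayed return of GI function to nausea and vomiting and to a longer stay, and nausea, vomiting and constipation are all in the transient row. The toxicity row is limited to 2 h, while adverse events are collected to the 30th post-operative day, so a later suspected reaction has to be placed in another row.

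**Step 5. Result.** For a serious suspected reaction in the two rows, the per-event assessment calls it serious and related, and the table sends it to the log alone. The passages disagree.

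**The case against.** The strongest reply is that Table 2 is captioned as event recording. It says where an event is written down and does not replace the assessment of seriousness, causality and expectedness, which the next paragraph requires for every adverse event. On that reading a log entry and an SAE form can coexist, and the sponsor's duty covers all rows. The article also condenses a full protocol that it describes as available as a supplement, and the reporting procedure may be complete there.

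Much of this stands. A reader might infer that the section has no seriousness step and that serious reactions in these rows can never become SARs or SUSARs. The documents do not support that, because the assessment exists and exempts nothing.

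A reader might also point to drug-treated arrhythmia as the event that slips through. The intervention description ties arrhythmia to systemic toxicity, and toxicity within 2 h of infusion belongs in the row that has the seriousness condition. The example therefore does not carry the point.

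Nor can the problem be sized by multiplying a guessed rate by the number of patients per arm, since the documents give no rate of serious related events in these rows.

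The reply does not remove the conflict itself. The article prints a rule for these two rows and calls the table the specific requirements. That is a statement that disagrees with its neighbour, not a detail left to a longer document.

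**Conclusion.** The point holds as an inconsistency between Table 2 and the per-event assessment text, confined to two of six rows and to events thought to be adverse reactions. A site that follows the table literally could log a serious suspected reaction without escalating it. The possible consequences are delayed or missed expedited reports and an under-count of SARs. The events are not lost: they stay on the adverse event log in both blinded arms and remain available for comparison.

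The conclusion assumes that some events in these rows can meet the criteria for serious, and that at least some sites use the table as their working instruction. How many events this would touch cannot be estimated from the documents. It is a should-fix matter of reconciling two passages and does not show that safety oversight fails.

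**What to change.** Reconcile the passages in Table 2, using the trial's own terms, after checking what the full protocol says for the same rows.

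- In the suspected-reaction cells for transient events and for grade 1/2 complications, keep the log entry and add the toxicity row's condition, "if meets criteria for serious", followed by the action already used for grade 3+: "Record as SAR/SUSAR; report to sponsor within 24 h of becoming aware".
- Add the same 24 h clause to the lidocaine-toxicity cell, so that all rows with a serious suspected reaction carry the same timing.
- Leave the column for events not thought to be reactions as it is. This keeps the evident aim of not escalating common surgical events that are unrelated to the drug.

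The cost is wording in three cells, a short note to sites, and probably a few extra expedited reports. Outcome definitions, data collection and the planned analyses do not change.
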